## Abstract

**Background:**

X-ray mammography remains the predominant test for screening for breast cancer, with the aim of reducing breast cancer mortality. In the English NHS Breast Screening Programme each woman’s mammograms are examined separately by two expert readers. The two readers read each batch in the same order and each indicates if there should be recall for further tests. This is a highly skilled, pressurised, repetitive and frequently intellectually unchallenging activity where readers examine one or more batches of 30–50 women’s mammograms in each session. A vigilance decrement or performance decrease over time has been observed in similar repetitive visual tasks such as radar operation.

**Methods/Design:**

The CO-OPS study is a pragmatic, multi-centre, two-arm, double blind cluster randomised controlled trial of a computer software intervention designed to reduce the effects of a vigilance decrement in breast cancer screening. The unit of randomisation is the batch. Intervention batches will be examined in the opposite order by the two readers (one forwards, one backwards). Control batches will be read in the same order as one another, as is current standard practice. The hypothesis is that cancer detection rates will be higher in the intervention group because each readers’ peak performance will occur when examining different women’s mammograms. The trial will take place in 44 English breast screening centres for 1 year and 4 months. The primary outcome is cancer detection rate, which will be extracted from computer records after 1 year of the trial. The secondary outcomes include rate of disagreement between readers (a more statistically powerful surrogate for cancer detection rate), recall rate, positive predictive value, and interval cancer rate (cancers found between screening rounds which will be measured three years after the end of the trial).

**Discussion:**

This is the first trial of an intervention to ameliorate a vigilance decrement in breast cancer screening.

**Trial registration:**

ISRCTN46603370 (submitted: 24 October 2012, date of registration: 26 March 2013).

## Background

### Epidemiology and burden of breast cancer

Breast cancer is a leading cause of mortality in women and was the cause of death for 10,280 women in England and Wales in 2010. It was responsible for 12% of all deaths of women in their 50s and 8% of deaths of women in their 60s [1].

In England, up to 2.3 million women aged 47 to 73 years are projected to have breast cancer screening each year [2,3]. The recall rate is 40 per 1,000 women screened, and the cancer detection rate is 7.8 per 1,000 women screened; therefore, 32 healthy women per 1,000 screened are recalled for further tests (false-positive recalls) [3].

Currently, 66% of all breast cancers in women 50 to 64 years of age in England are detected by screening [3]. This occurs because some women choose not to be screened and the screening test is not perfect. Cancers diagnosed between screens (interval cancers) either grow *de novo* between screening rounds or are not seen or picked up by the programme. As with all screening programmes, the National Health Service Breast Screening Programme (NHSBSP) aims to keep interval cancers to a minimum, with a target rate of 2.3 per 1,000 women [4,5]. However, these are difficult targets; the rates achieved are closer to 3 per 1,000 women [6].

When investigating methods of improving cancer detection, one has to be mindful of the potential for increasing overdiagnosis and overtreatment (that is, cancers detected at screening and treated which never would have presented or caused problems within the patient’s life). It is important to ensure that any additional test or new methodology that increases cancer detection has a matched fall in interval cancer rates.

### Existing knowledge

In the NHSBSP, each woman’s mammograms are examined separately by two specialists, each of whom indicates whether there should be a recall for further tests. These experts are radiologists, advanced radiography practitioners or breast clinicians, (henceforth referred to for simplicity as *readers*). If the two readers disagree, the case is referred for arbitration, usually by a third reader or a group of readers. For workflow reasons, 30 to 50 women’s mammograms are grouped together into a batch and are typically read without a break. In a mammography reading session, a reader may examine one, two or more batches. On average, readers assess two women’s mammograms per minute [7]. This is a highly skilled, pressurised and repetitive, but frequently intellectually nonchallenging, activity. A vigilance decrement manifesting as a performance decrease over time has been observed in a wide range of similar repetitive visual tasks such as radar operation [8].

Current practice is for both readers to examine each batch of mammograms in the same order as one another; thus any vigilance decrement will occur when reading the same woman’s mammograms. We hypothesise that presenting batches to the first and second readers in a different order from one another may increase the sensitivity of screening. A trial is required to determine whether such improvements would be realised in practice.

## Methods/Design

Our hypothesis is that if the second reader examines the batch of mammograms in the order opposite that of the first reader, the overall cancer detection rates will increase. This will happen through increasing rates of disagreement between readers because each reader’s peak performance will occur when examining different cases.

The trial will be carried out in accordance with Good Clinical Practice (GCP) as detailed in the Medical Research Council GCP guidelines [9] and the following protocol. The trial will be reported in line with the CONSORT (Consolidated Standards of Reporting Trials) statement [10] and the further guidance available for cluster randomised controlled trials [11]. Ethical approval was granted by the Coventry and Warwickshire National Health Service (NHS) Research Ethics Committee on 27 June 2012 (Reference 12/WM/0182). Formal approval was also granted by the Research and Development office of each NHS Trust involved in the study.

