### Trial summary

The trial is a pragmatic, multicentre, two-arm, double-blind, cluster randomised controlled trial of a computer software intervention designed to reduce the effects of a vigilance decrement in breast cancer screening. The intervention changes the order in which the readers examine the batches of mammograms. The centres will be NHSBSP centres with digital mammography equipment. A cluster for randomisation comprises a batch of mammograms (approximately 30 to 50 women’s mammograms). Intervention batches will be examined in the opposite order by the two readers (one in appointment order and one in reverse appointment order). Control batches will be read in the same order as one another as is current standard practice. The unit for analysis is the individual woman’s outcome.

Standard practice is for both readers to read the batch of mammograms in the order in which the women were booked in for their appointments. In the control group, both readers will read each batch in the same order as one another, but this may be in appointment order or in reverse appointment order (↓↓ or ↑↑). In the intervention group, both readers will read the mammograms in the order opposite one another (↓↑ or ↑↓). This design blinds the readers because if they read in the reverse order, they will not know if they are reading the intervention or control group. The study software which will be used to run the trial will be embedded in the National Breast Screening Service (NBSS) software system in every English breast screening centre as part of routine updating of the NBSS system.

The pilot study will be conducted in three screening centres for 2 weeks to ascertain practical issues with implementation and to test the data collection tool, which will extract the results from the screening centres’ electronic database (NBSS). Concurrently, a survey of all English breast screening centres will be conducted to ascertain key characteristics relevant to the trial which may differ between centres, such as the method of arbitration used. These details will be described in the report and considered in the statistical analysis of the trial to ascertain whether the effectiveness of the intervention is affected by these characteristics.

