### Trial aims and outcomes

The primary aim of the trial is to determine whether presenting the cases to the first and second readers in the order opposite one another increases the cancer detection rate (true-positive rate). The secondary aims and outcome measures of the trial are as follows:

1. Is there a difference in the number of disagreements between readers in each study arm? This is the proposed mechanism by which an increase in cancer detection rate occurs and therefore acts as a surrogate outcome, particularly if the effect size is smaller than anticipated or recruitment targets are not met. The rate of disagreement refers to the proportion of cases for which one reader thought the case should be recalled and the other reader thought the case should not be recalled.

2. Is there a difference in 3-year interval cancer rate in each study arm? Furthermore, as the interval cancer rate can be considered an approximation of the false-negative rate, is this change (if any) concurrent with changes in the cancer detection rate between study arms (primary outcome)? The interval cancer rate is measured as the rate of cancers detected symptomatically in the 3 years subsequent to screening and therefore will be collected 3 years after the trial implementation is complete.

3. Do the recall rate and positive predictive value (PPV) differ between the study arms?

4. With regard to NHS considerations, is the intervention cost-effective when compared with the control arm? The lifetime cost-effectiveness of the intervention will be modelled using the primary outcome from the trial. Are there any effects introduced by the trial methodology? Specifically, are the cancer detection and recall rates affected by introducing reverse reading order? The cancer detection rate and the recall rate for both versions of the control arm (↓↓ and ↑↑) will be compared to measure any adverse effects of reading in reverse order.

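### Reader disagreement is called the mechanism and surrogate for cancer detection, and a possible primary outcome, without the arbitration condition this needs

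*Protocol article*

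**What the plan says.** Under Methods/Design, the article explains how opposite-order reading should raise detection: "This will happen through increasing rates of disagreement between readers". The reason it gives is that the two readers' peaks will fall on different cases. Under Existing knowledge it describes what follows a disagreement: "If the two readers disagree, the case is referred for arbitration, usually by a third reader or a group of readers".

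Secondary aim 1, under Trial aims and outcomes, calls disagreement the proposed mechanism and, for that reason, a surrogate outcome. It defines the rate over every woman screened, as "the proportion of cases for which one reader thought the case should be recalled and the other reader thought the case should not be recalled". The Discussion goes further: an effect too small to show in detection would show in disagreement, and disagreement may have to serve as the primary outcome if recruitment targets are missed.

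Arbitration appears once more. Under Trial summary, a survey will record centre characteristics, "such as the method of arbitration used" being the example, and these will be "considered in the statistical analysis of the trial to ascertain whether the effectiveness of the intervention is affected by these characteristics". The article makes no statement about how often arbitration recalls a cancer that only one reader flagged.

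**The concern.** A cancer flagged by one reader counts as detected only if arbitration recalls it. Moving the two readers' peaks to different cases has two effects on women with cancer. Some cancers that both readers would have missed are now flagged by one. Some that both would have recalled are now also flagged by only one, and their recall comes to depend on arbitration. Both effects raise disagreement, but only the first adds cancers.

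Disagreement therefore fixes neither the size nor, on its own, the sign of a change in detection. The definition in secondary aim 1 widens the gap because it counts disagreements about women without cancer in the same rate. What is at stake is the reading of secondary aim 1. If the fallback in the Discussion were used, the trial's headline result would also rest on it.

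**Working it through.** **Plan's own figure.** Two proportions, 7.8 against 8.3 per 1,000, two-sided 5%, 80% power, equal arms: 501,398 per arm by the standard normal formula, against 501,361 in Power and sample size. The figure reproduces. The later inflation for clustering is meant to restore this effective size, so 501,361 per arm is used below.

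**Are reader averages the same in both arms?** Under Recruitment and randomisation, batches go with equal probability to four groups (↓↓, ↑↑, ↓↑, ↑↓). In each arm the first reader reads half the batches in each direction, and so does the second. Under Blinding, readers do not know the arm. Each reader's average detection should therefore be equal between arms.

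**Formula.** Among women with cancer, let B, S and N be the proportions recalled by both readers, one reader and neither.

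- B + S + N = 1.
- The two readers' detection rates sum to 2B + S, which is fixed.
- If S rises by D, B falls by D/2 and N falls by D/2. This does not require the readers to be independent.
- Detection after arbitration is B + aS, so it changes by −D/2 + aD = **D × (a − 0.5)**. Here a is taken as equal in both arms.

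**Check of the split.** Assume a 40-case batch, sensitivity falling linearly from 0.9 to 0.7, and readers independent given position.

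| Among cancers | Both | One | Neither |
|---|---|---|---|
| Same order | 0.6435 | 0.3130 | 0.0435 |
| Opposite order | 0.6365 | 0.3270 | 0.0365 |
| Change | −0.0070 | +0.0140 | −0.0070 |

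Detection per cancer changes by −0.0028, 0, +0.0028 and +0.0056 at a = 0.3, 0.5, 0.7 and 0.9, as the formula gives.

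**Size against the planned effect.** The documents do not give a, so a range is shown. The second column is the rise in disagreement among women with cancer, per 1,000 screened, needed for the planned +0.5, that is 0.5/(a − 0.5). The last two columns fix that rise at 1.0 per 1,000, which is enough for +0.5 if arbitration is perfect. Power is at 501,361 effective women per arm.

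| a | D needed for +0.5 | Gain if D = 1.0 | Power if D = 1.0 |
|---|---|---|---|
| 1.0 | 1.00 | 0.50 | 80% |
| 0.9 | 1.25 | 0.40 | 61% |
| 0.8 | 1.67 | 0.30 | 39% |
| 0.7 | 2.50 | 0.20 | 20% |
| 0.6 | 5.00 | 0.10 | 8% |
| 0.5 | none suffices | 0 | – |

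**Pooling.** With 7.8 screen-detected cancers per 1,000, about 992 of every 1,000 women have none. A rise in the pooled rate may lie largely among them, where it adds no cancers whatever a is.

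**The case against.** The strongest case on the other side has four parts.

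- **The main answer is safe.** The primary outcome is detection after arbitration, tested two-tailed, so a net loss of cancers would count against the intervention. This stands. A reader might infer that the trial has no endpoint for cancers lost at arbitration, and the documents do not support that.
- **Other endpoints help to explain a flat result.** Disagreement itself separates an intervention that changed nothing from one that raised disagreement without raising detection. Recall rate, positive predictive value and interval cancers add to this, and the planned analysis by arbitration method bears on arbitration as a modifier. A reader might infer that no planned endpoint could show why detection stayed flat, which is too strong. The limit is that the arbitration-method analysis compares centres and does not record what happened to single-flagged cancers.
- **A fall in detection is only a possibility.** It needs a below 0.5, and nothing in the article suggests that. Above 0.5 the direction given under Methods/Design is right but the gain is diluted. The effect may also be small. Assuming 10.8 cancers per 1,000 (7.8 screen-detected plus about 3 interval), the 40-case example gives D of 0.0140 × 10.8 = 0.15 per 1,000, and a loss at a = 0.3 of 0.0028 × 10.8 = 0.03 per 1,000. That example shows how the split works; it does not forecast harm.
- **A breakdown by reader concordance is analysis-plan detail.** It may be in the analysis plan, which is not shown, so its absence from the article is not the point made here. What the article does state is the surrogate claim and the fallback to disagreement as primary, both without the condition they need.

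Replacing all-women disagreement with cancers flagged by at least one reader is also tempting. In the same example that outcome rises by D/2, about 0.08 per 1,000, for which power would be well under 10%, and its interval-cancer part would wait three years. The replacement is not recommended.

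**Conclusion.** The concern holds in a narrow form. The article presents disagreement as the route to higher detection, as its surrogate and as a possible primary outcome. The link requires arbitration to recall more than half of single-flagged cancers, and the size of any gain scales with a − 0.5. A rise in disagreement among cancers that would give +0.5 per 1,000 under perfect arbitration gives +0.4 at a = 0.9 and +0.2 at a = 0.7. The pooled endpoint can also rise among women without cancer and carry no gain.

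The result rests on equal average reader detection in the two arms, which the balanced four-group randomisation and blinding support, and on a being the same in both arms. If cancers newly split between readers are easier or harder for arbitration than other single-flagged cancers, the dilution will differ from the table.

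The documents do not support saying that detection will stay flat or fall, or that the primary outcome or sample size is wrong for this reason.

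**What to change.** 1. Keep cancer detection as the primary outcome and all-women disagreement as a secondary outcome.
2. In Methods/Design, secondary aim 1 and the Discussion, state that more disagreement raises detection only if arbitration recalls more than half of the cancers flagged by one reader, with reader averages unchanged.
3. State that a rise in all-women disagreement will not by itself be interpreted as a rise in detection, nor be grounds for making disagreement the primary outcome.
4. Add a supportive tabulation by arm of screen-detected cancers recalled by both readers, and of those flagged by one reader and recalled at arbitration. When the 3-year data arrive, add interval cancers that one reader flagged but that were not recalled.

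The cost is some rewording and a few tables. The reader opinions and cancer outcomes are already needed for the planned endpoints. The tabulation is descriptive and has low power. Its interval-cancer part waits for the planned extract and will include cancers that arose after screening, for which a reader's flag may be unrelated. The article would also have to make a less favourable statement about its surrogate.

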### Trial summary

The trial is a pragmatic, multicentre, two-arm, double-blind, cluster randomised controlled trial of a computer software intervention designed to reduce the effects of a vigilance decrement in breast cancer screening. The intervention changes the order in which the readers examine the batches of mammograms. The centres will be NHSBSP centres with digital mammography equipment. A cluster for randomisation comprises a batch of mammograms (approximately 30 to 50 women’s mammograms). Intervention batches will be examined in the opposite order by the two readers (one in appointment order and one in reverse appointment order). Control batches will be read in the same order as one another as is current standard practice. The unit for analysis is the individual woman’s outcome.

Standard practice is for both readers to read the batch of mammograms in the order in which the women were booked in for their appointments. In the control group, both readers will read each batch in the same order as one another, but this may be in appointment order or in reverse appointment order (↓↓ or ↑↑). In the intervention group, both readers will read the mammograms in the order opposite one another (↓↑ or ↑↓). This design blinds the readers because if they read in the reverse order, they will not know if they are reading the intervention or control group. The study software which will be used to run the trial will be embedded in the National Breast Screening Service (NBSS) software system in every English breast screening centre as part of routine updating of the NBSS system.

The pilot study will be conducted in three screening centres for 2 weeks to ascertain practical issues with implementation and to test the data collection tool, which will extract the results from the screening centres’ electronic database (NBSS). Concurrently, a survey of all English breast screening centres will be conducted to ascertain key characteristics relevant to the trial which may differ between centres, such as the method of arbitration used. These details will be described in the report and considered in the statistical analysis of the trial to ascertain whether the effectiveness of the intervention is affected by these characteristics.

The trial will last 16 months in 44 centres and will include all women attending routine digital mammography screening during the study period. The data gathered during the first 12 months (1.1 million women) will be derived from the NBSS database to determine whether the intervention has increased the cancer detection rate. These data will include all items for the primary and secondary analyses, with the exception of interval cancer rate. The interval cancer data will be collected 3 years after the end of the study period to ascertain whether there has a been a decrease in the rate of interval cancers and therefore whether the intervention reduced the number of cancers missed at screening.

### Trial aims and outcomes

The primary aim of the trial is to determine whether presenting the cases to the first and second readers in the order opposite one another increases the cancer detection rate (true-positive rate). The secondary aims and outcome measures of the trial are as follows:

1. Is there a difference in the number of disagreements between readers in each study arm? This is the proposed mechanism by which an increase in cancer detection rate occurs and therefore acts as a surrogate outcome, particularly if the effect size is smaller than anticipated or recruitment targets are not met. The rate of disagreement refers to the proportion of cases for which one reader thought the case should be recalled and the other reader thought the case should not be recalled.

2. Is there a difference in 3-year interval cancer rate in each study arm? Furthermore, as the interval cancer rate can be considered an approximation of the false-negative rate, is this change (if any) concurrent with changes in the cancer detection rate between study arms (primary outcome)? The interval cancer rate is measured as the rate of cancers detected symptomatically in the 3 years subsequent to screening and therefore will be collected 3 years after the trial implementation is complete.

3. Do the recall rate and positive predictive value (PPV) differ between the study arms?

4. With regard to NHS considerations, is the intervention cost-effective when compared with the control arm? The lifetime cost-effectiveness of the intervention will be modelled using the primary outcome from the trial. Are there any effects introduced by the trial methodology? Specifically, are the cancer detection and recall rates affected by introducing reverse reading order? The cancer detection rate and the recall rate for both versions of the control arm (↓↓ and ↑↑) will be compared to measure any adverse effects of reading in reverse order.

